## Abstract

**Background:**

South Africa remains the global epicentre of HIV infection, and adolescent women have the highest incidence of HIV in the country. South Africa also has high rates of alcohol and other drug (AOD) use, violence, and gender inequality. Violence converges with AOD use, gender inequities and other disparities, such as poverty, to increase sexual risk and poor educational attainment for adolescent women. This study seeks to test the efficacy of peer recruitment and cofacilitation of the Young Women’s Health CoOp (YWHC), a comprehensive gender-focused intervention to reduce HIV risk behaviours and increase the uptake of HIV counselling and testing (HCT) among out-of-school, adolescent women who use AODs. The YWHC is facilitated by local research staff and supported by peers.

**Methods:**

This cluster-randomised trial is enrolling participants into two arms: a control arm that receives standard HCT, and an intervention arm that receives the YWHC. Participants are enrolled from 24 economically disadvantaged communities in Cape Town, South Africa. These geographically distinct communities serve as clusters that are the units of randomisation. This study uses adolescent peer role models and research field staff to recruit marginalised adolescent women. At baseline, participants complete a questionnaire and biological testing for HIV, recent AOD use, and pregnancy. The core intervention is delivered in the month following enrollment, with linkages to health services and educational programmes available to participants throughout the follow-up period. Follow-up interviews and biological testing are conducted at 6 and 12 months post enrollment.

**Discussion:**

The study findings will increase knowledge of the efficacy of a comprehensive HCT, gender-focused programme in reducing AOD use, victimisation, and sexual risk behaviour and increase uptake services for out-of-school, adolescent women who use AODs. The trial results could lead to wider implementation of the YWHC for vulnerable adolescent women, a key population often neglected in health services.

**Trial registration:**

Trial registration no: NCT02974998, November 29, 2016.

## Background

South Africa is the global epicentre of HIV infection, with an estimated 7.1 million people living with HIV [1]. HIV prevalence among South African youth is among the world’s highest [2], with prevalence rising rapidly throughout adolescence [3]. Adolescent women in South Africa are disproportionately affected by HIV, having the highest incidence in the country [4]. Young women aged 15 to 19 are estimated to have an HIV prevalence eight times that of young men in the same age group [5].

A major driver of HIV risk in this group is alcohol and other drug (AOD) use. AOD use among South African youth is a pressing public health concern [6], particularly the use of alcohol, cannabis, and methamphetamine (“tik”) among Cape Town youth [7–9]. The South African National Youth Risk Behaviour Survey (YRBS) found that among female high school learners in the Western Cape, 21.1% had used cannabis in their lifetime, with 12.1% reporting use in the past month; 6.6% reporting lifetime tik use; and 40.1% reporting having engaged in binge drinking in the past month [6]. These high rates of AOD use are particularly alarming because AOD use is a known contributor to the risks associated with acquiring HIV [7, 10]. Additionally, previous studies suggest that adolescents who use AODs are at an increased risk of dropping out of school [7, 11–14].

South Africa also has high rates of violence, including gangsterism and gender-based violence (GBV) [15–17]. Exposure to violence, particularly sexual violence, converges with AOD use, social gender inequities and other disparities, such as poverty, to increase sexual risk and poor educational attainment for adolescent women [16, 18–20]. These factors contribute to the high rate of school dropout among youth [14], with an estimated 44% of South African adolescents not completing high school [21, 22]. Cape Town, in particular, has a school dropout rate of 54.9% among adolescents [19].

Gender inequality plays a key role in school dropout among adolescent women [23, 24], who are often discouraged from taking advanced-level courses and are expected to maintain domestic roles [24]. Additionally, they often report experiencing GBV, sexual abuse, and teenage pregnancy; the inability to afford school fees or transportation; participation in gangs or being in relationships with gang members; and AOD use as reasons for dropping out of school [9, 16, 18, 23]. Having peers who use AODs and engage in risky sexual behaviours can also have a detrimental impact on school dropout [14].

Adolescent women who drop out of school contend with unique consequences. For example, they face a higher probability of heavy alcohol or illicit drug use, which exacerbates their risk for victimisation, pregnancy, and HIV [9, 14, 16, 25]. They may also face limited employment opportunities because of their lack of education or skills training [14]. Because of the need for financial stability, young women may become financially dependent on their partners or choose to support themselves, their families, or their AOD use through trading sex, sex with older men (often referred to as “blessers”), or involvement with gangs or having relationships with gang members [14, 26, 27].

Adolescent women in South Africa who drop out of school face multiple risks, including those fuelled by historical gender biases. For example, they may experience stigma in seeking services, as many clinics do not practise anonymity or they may treat women who use AODs with disrespect [28]. Additionally, this hard-to-reach, key population remains underserved by HIV and substance abuse rehabilitation programmes and health services [29].

To date, there have been no comprehensive, evidence-based HIV counselling and testing (HCT) programmes that address these intersecting contextual and behavioural risks for HIV among out-of-school, adolescent women who use AODs [30]. All of these barriers contribute to low HIV testing uptake and adherence among South African adolescents [31], with between 25% and 35% of adolescent women currently being tested for HIV [32, 33].

This study builds on a formative study (supplement to R01DA032061) that seeks to alleviate these barriers by using a combination of peer recruitment and outreach to increase uptake of HCT, and to test the efficacy of an adapted comprehensive gender-focused intervention, the Young Women’s Health CoOp (YWHC), which targets vulnerable adolescent women in disadvantaged communities in Cape Town who use AODs and have dropped out of school. The YWHC is based on an adaptation of several iterations of the original best-evidence Women’s CoOp intervention [34, 35]. The adapted South African iteration, the Women’s Health CoOp (WHC) is the only intervention that addresses the intersection between AOD use, victimisation, and sexual risks for HIV [36–40]. The WHC has been shown to be particularly effective in reducing AOD use and enhancing empowerment through HIV risk reduction and skills building.

## Methods/Design

### Objectives

One aim of this study is to train and evaluate adolescent peer role models contracted from the government to market and conduct community outreach with established outreach workers to recruit 500 out-of-school adolescent women who use AODs, and to cofacilitate the YWHC. Another aim is to test the efficacy of the YWHC for reducing AOD use, victimisation, and sexual risk behaviour (primary outcomes) and improving access to effective treatment and support services through linkages to care (substance abuse rehabilitation, HIV, sexually transmitted infections [STIs], antenatal and reproductive health services as secondary outcomes) relative to standard HCT for adolescent women.

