### Cluster randomisation

We selected 12 clusters for each of the two geographic areas. Within each block of 12, clusters were randomised to one of the two arms, with equal allocation. Additionally, 5 replacement clusters were selected (3 within the Coloured geographic area and 2 within the Black African geographic area). These replacement clusters will be used if any of the selected clusters are deemed unusable prior to conducting outreach and recruitment in a specific cluster. At times, gangs are very violent, making outreach and recruitment dangerous, even during the day. If this persists in a community, it will need to be replaced for the purposes of this study.

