### Study procedures

#### Recruitment

The study uses female adolescent peer role models (aged 18 to 25) called Expanded Public Works Programme (EPWP) beneficiaries in combination with trained outreach workers to assist in reaching and recruiting participants. The peer EPWP beneficiaries are selected each year with help from the Western Cape Department of Social Development. They are trained on a series of topics, including professionalism, job expectations, AOD use, gender awareness, and community engagement. The EPWP beneficiaries also receive certification in a simplified Collaborative Institutional Training Initiative (CITI) training for human subjects and obtain training on completing daily outreach reports. Trained study outreach workers—who have worked in and around the target communities and are familiar with community outreach methods—offer oversight to the EPWP beneficiaries. The purpose of this team effort is to reach adolescent women who have dropped out of school and are using AODs. The trained study outreach workers conduct the screening with adolescents who they have identified during outreach, or the EPWP beneficiaries have referred them to, to ensure privacy and confidentiality. Study staff are multilingual in English and Afrikaans and/or isiXhosa.

Outreach is conducted in areas of high target population density in the selected communities. Trained EPWP beneficiaries and study staff post recruitment cards and fliers in their targeted communities, paying special attention to establishments where adolescent women who are out of school are known to frequent, such as community centres or libraries. Marketing about the study is conducted by walking through the neighbourhoods looking for adolescent women who may be hanging out near tuck shops (small, food-selling vendors), corners, and hair and nail salons; and by talking with community members. Potential participants who either contact project staff using the numbers given on the recruitment cards and fliers or who are approached through outreach are screened for eligibility by study staff.

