#### Intake assessment

Participants are transported to a secure field site for all study activities. After final eligibility is determined through a rescreening, consent and/or assent is obtained, participants take a breathalyser test for recent alcohol use, locator information is collected, and a photograph of the participant is taken (which is returned at the final appointment). At this first appointment, participants complete the baseline questionnaire via computer-assisted personal-interviewing (CAPI) technology, and audio computer-assisted self-interviewing (ACASI) in their home language (English, Afrikaans, or isiXhosa) for sensitive topics, such as experiences of abuse. Staff then collect biological specimens to conduct pregnancy testing, screening for recent drug use, and rapid HIV testing. A urine specimen sample is collected to perform rapid tests to detect metabolites of recent use of cocaine, methamphetamines, amphetamines, opioids, ecstasy, and marijuana via a 5-panel drug screening test. Methaqualone (Mandrax) is measured through a separate urinalysis test. Two rapid tests are conducted for HIV testing; if a participant has a positive test result for either test, she receives a third test and posttest counselling in accordance with the national South African standards. If two tests show a positive HIV result, the participant is considered to have a positive test. All staff undergo training for biological specimen collection and are certified to conduct rapid HCT. All positive HIV screening determinations or positive test results for pregnancy are referred to the local health clinic regardless of study arm. For other services needed, participants in the intervention arm receive active referrals, whereas participants in the HCT control arm receive passive referrals.

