### Staff training

The intervention facilitators, including the EPWPs, are trained by the Principal Investigator or the South African Project Director on the intervention workshops. All project staff involved are trained on the research methods, data collection, and issues surrounding confidentiality. Further, all field staff receive a field manual and training on safety and security procedures, protection of human subjects, and how to conduct active and passive referrals.

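### Women are recruited after their cluster is randomised, by discretionary outreach done partly by peers who as a group also cofacilitate the intervention, so who enrols may differ by arm

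*Protocol article*

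**What the plan says.** **Order of events.** Cluster randomisation is reported as done: "Within each block of 12, clusters were randomised to one of the two arms, with equal allocation". A selected community can be replaced if "deemed unusable prior to conducting outreach and recruitment in a specific cluster", so outreach in a community comes after its selection and allocation.

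**How women are found.** Under Recruitment, peers (the EPWP beneficiaries) are used "in combination with trained outreach workers to assist in reaching and recruiting participants". Outreach consists of cards, fliers and walking through neighbourhoods to places where out-of-school young women gather. No list or sampling frame of eligible women is described.

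**Who screens and enrols.** "The trained study outreach workers conduct the screening with adolescents who they have identified during outreach, or the EPWP beneficiaries have referred them to". Intake assessment then puts a rescreening and consent or assent at the field site before the baseline questionnaire and biological tests.

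**The peers' second role.** Objectives has the peers help "recruit 500 out-of-school adolescent women who use AODs, and to cofacilitate the YWHC". Staff training counts them among the facilitators: "The intervention facilitators, including the EPWPs, are trained by the Principal Investigator". The workshops belong to the intervention arm only (Study activities by arm).

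**Arm-dependent intake.** Positive HIV or pregnancy results lead to a clinic referral in both arms. For other services, "participants in the intervention arm receive active referrals, whereas participants in the HCT control arm receive passive referrals". The Intervention arm section confirms that active referrals are already offered at intake.

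**Analysis.** The primary models adjust for the baseline value of the outcome (Analysis).

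**The concern.** Randomising communities balances communities. It does not balance the women later chosen from them, because that choice is made after allocation and involves judgement about whom to approach and encourage. The people making part of that choice belong to a group that also helps to run the workshops, and the workshops exist in one arm only. Women can also accept or decline because of what their community is being offered. The Discussion itself suggests that using peers to recruit and cofacilitate may make the intervention more attractive and participation more likely. If that attraction acts on enrolment, it can act in one arm only.

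At stake is the comparability of the arms. If women readier to change, or at lower risk, enter the intervention arm more often, part of the observed difference is selection. Intention-to-treat analysis does not help, because the selection precedes entry. Baseline adjustment removes part of an imbalance in the measured outcome, but not one in motivation or willingness to attend a group.

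**Working it through.** The finding rests on the sequence and the roles set out above. The arithmetic only shows what a plausible imbalance could do.

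**Inputs from Sample size and power:** 225 women per arm at 12 months, 24 clusters (12 per arm), ICC 0.01, two-sided α 0.05, power 0.80, detectable difference 0.13 at a condom-use proportion of 0.6.

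**Step 1: the plan's own figure.**
- Women analysed per cluster: 225/12 = 18.75.
- Design effect: 1 + (18.75 − 1) × 0.01 = 1.1775.
- Effective size per arm: 225/1.1775 = 191.1.
- Detectable difference: Δ = 1.96 × √[2p̄(1 − p̄)/191.1] + 0.842 × √{[p₁(1 − p₁) + p₂(1 − p₂)]/191.1}, with p̄ the mean of p₁ and p₂.
- Upward from 0.6 this gives Δ = 0.1346, which agrees with the stated 0.13 after rounding. Downward from 0.6 it gives 0.143.

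**Step 2: standard error of the arm difference, two ways.**
- Implied by the stated figure: 0.13/(1.96 + 0.84) = 0.0464.
- Directly from the stated design at p = 0.6: √(2 × 0.6 × 0.4 × 1.1775/225) = 0.0501.

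**Step 3: false difference from unequal recruitment.** Bias = (difference between arms in the share of a subgroup) × (difference in outcome between that subgroup and other women). It is the difference in share between arms that matters, not the share in one arm. Neither factor is in the documents; both are assumptions.
- 10 points × 0.20 = 0.02.
- 20 points × 0.20 = 0.04, which is 0.04/0.13 = 31% of the difference the trial is sized to detect.

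**Step 4: two-sided error when the intervention has no effect.** Error = 1 − Φ(1.96 − b/SE) + Φ(−1.96 − b/SE), where b is the bias.

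| Bias b | SE 0.0464 | SE 0.0501 |
|---|---|---|
| 0 | 5% | 5% |
| 0.02 | 7.2% | 6.8% |
| 0.04 | 13.8% | 12.6% |

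**Step 5: wider range.** With share differences of 5 to 20 points and outcome differences of 0.2 to 0.4, using SE 0.0501, the bias runs from 0.01 to 0.08 and the error from about 5.5% to 36%.

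All of these errors are for a comparison without baseline adjustment.

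**Overlap of recruiting and facilitating.** 500 women in 24 clusters is about 21 per cluster. Workshop groups hold up to eight, so a cluster needs at least three groups if groups form within clusters (an inference). Sessions start about a week after intake (Fig. 1 note). Unless a cluster's recruitment closes within about a week, workshops for it run while recruitment continues.

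**The case against.** **Peers do not screen or enrol.** A reader might infer that they do. Recruitment gives screening to outreach workers and study staff, and rescreening at the field site precedes consent. This stands. The peers' influence is limited to who is approached and referred, and the point is worded accordingly.

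**Same-cluster conflict is not shown.** Nothing says that a peer cofacilitates for the community in which she recruits. The dual role is given to the peers as a group, and the Abstract has research staff facilitating with peer support. A rota separating the two tasks may already exist. This stands too.

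**Knowledge of arm at screening is not shown.** One might infer that intake staff must know the arm when they screen and consent. The article mentions arm-specific referrals only after describing those steps and does not say who makes them. Late disclosure may already be practice.

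**Silence is not evidence.** Masking, scripts and rotas could sit in the procedural manual or field manual that the article names. Agreed: absent masking is not the finding. The finding rests on what is stated, namely recruitment after allocation, discretionary outreach, the peers' two roles and referrals that differ by arm.

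**The bias could be small or reversed.** Every woman must report recent condomless sex and qualifying alcohol or drug use, which limits how many low-risk women can enter. Outreach in risky settings could also over-select higher-risk women. This stands, so neither size nor direction can be asserted.

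**Late disclosure may leak.** Allocation is by community, so word of mouth can reveal it. This limits the fix without removing its value.

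**Conclusion.** The point holds as a design risk. Women are identified and recruited after their community is allocated, by discretionary outreach in which peers who as a group also cofacilitate the intervention take part, and intake referrals differ by arm. Who is approached, referred and enrolled may therefore differ by arm and may bias the outcome comparisons. Adjusting for the baseline outcome deals with only part of this.

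The documents do not support saying that every outcome is biased, or that the trial's error rate is 14%. The range of about 7% to 14% assumes a 10 to 20 point difference between arms in the share of a subgroup whose condom use is 0.20 higher, and no baseline adjustment; the planned models would reduce it to the extent that the baseline outcome captures the imbalance. The conclusion does not depend on any one of these values. The change is worth making because enrolment is still open (Trial status).

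**What to change.** For the remaining enrolment:

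1. Use one arm-neutral recruitment script and flier in all clusters.
2. Disclose the arm, and open the referral and workshop step, only after consent and the baseline questionnaire are complete.
3. Roster the existing peers so that none recruits in a cluster while she cofacilitates for it.
4. Use the outreach counts already planned for Aim 1 to compare approached, eligible and consented numbers by arm, together with baseline characteristics. Add a sensitivity analysis of the primary models adjusted for prespecified baseline risk covariates.

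If the manuals already provide for any of items 1 to 3, stating so in the protocol is enough for that item.

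**Cost.** Existing staff can do this, with a revised procedure manual, a peer rota and a modest amount of extra analysis. Peer scheduling becomes less flexible. Item 2 may require revised consent and assent wording, including the in loco parentis process, and so ethics approval. Women already enrolled cannot be recruited again; for them only item 4 helps, and it can reveal measured imbalance but not unmeasured motivation.

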### Outcome measures

The primary outcomes of this study are reduced AOD use (as measured by AOD testing and by self-reported frequency of AOD use) and reduced sexual risk (as measured by condomless sex, self-reported number of casual partners, sex trading, and partner concurrency) in the past 30 days. We used the Revised Risk Behavior Assessment (RRBA) with youth measures to assess these outcomes. An additional outcome is reduced violence and victimisation in the last 3 months [42].

The secondary outcomes of this study include access to health services, as measured by self-reported use of sexual reproductive health services and HIV and STI testing services, linkage to HIV treatment and care services, and staging and antiretroviral therapy (ART) initiation, and advancement as it pertains to education and job training, as measured by enrollment in training certifications, self-reported motivation and perception regarding learning, and self-reported knowledge regarding strategies to improve educational outcomes.

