### Sample size and power

#### Power considerations for Aim 2

This study proposes several primary outcomes for Aim 2, and the power analysis were conducted to ensure that the study was adequately powered to detect intervention effects on these key outcomes, such as proportion of condom use (see earlier description of primary and secondary outcomes). The assumptions for this analysis are based on past studies of the WHC in South Africa and the Young Women’s CoOp pilot efficacy study conducted in the United States. In past studies, the proportion of condom use has ranged from 0.3 to 0.6. For all power analysis, we assumed a two-sided test with α = 0.05, a power of 0.8, and an intracluster correlation coefficient (ICC) estimate of 0.01. Based on these parameters, with a sample size of 225 per intervention arm at 12-month follow-up (an expected 90% follow-up) and 24 clusters, the minimal detectable difference is 0.13 for the outcome of condom use at the highest proportion of 0.6. For outcomes that may be less common overall, such as biologically confirmed HIV, we will be able to detect similar differences, ranging from 0.10 to 0.13.

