### Analysis

To address Aim 1, we will analyse data collected by both peer role models and project staff when conducting daily activities in the field. Simple descriptive data analysis will be used to answer this aim, such as counts of marketing materials distributed, counts of eligible young women introduced to project staff by peer role models and screened eligible. However, our primary analysis will test the hypothesis that the YWHC will reduce the primary outcome (sexual risk behaviour) as well as AOD use and victimisation relative to standard HCT (Aim 2: Hypothesis 1).

To test the efficacy of the intervention on each of these outcomes, we will use a standard intention-to-treat approach by including all participants as assigned to their study arm, regardless of their intervention exposure. The study design, which is longitudinal and clustered by community, creates an inherent multilevel structure, thereby introducing nonindependence. Consequently, our analytic strategy will be based on generalised linear mixed models, as use of hierarchical or multilevel mixed models allows for clustering due to community-level randomisation and repeated measures within individuals over time (at 6- and 12-month follow-up). Primary models will include a covariate for study arm, adjust for the baseline level of the outcome (e.g., heavy alcohol use), and account for community- and individual-level clustering. We will evaluate intervention effects individually at the two time points, initially by calculating proportions of the primary outcomes in the two randomised groups, with 95% confidence intervals. For multivariable modelling of intervention effects, we will use logit, Poisson, and linear regression approaches, as appropriate.

We will also test Hypothesis 2, which posits that the young women’s comprehensive HCT programme will improve the secondary outcome—access to HIV, STI, antenatal and reproductive health services—relative to standard HCT, using a similar data analysis approach. We will use a standard intention-to-treat analysis by including all participants as assigned to their study arm, regardless of their intervention exposure. The primary outcome of improved access will be operationalised in two ways: (1) a dichotomous measure of whether services were accessed (any and by type of service); and (2) a count of the number of times services were used during the 12-month follow-up period.

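### The protocol gives three incompatible definitions of the primary outcome and names no primary visit, so the trial's confirmatory claim is not fixed.

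*Protocol article*

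**What the plan says.** The protocol article describes the primary outcome in four places.

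- **Objectives.** The aim is to "test the efficacy of the YWHC for reducing AOD use, victimisation, and sexual risk behaviour (primary outcomes"). Three domains are primary, on an equal footing.
- **Outcome measures.** The first primary domain has two measures: "The primary outcomes of this study are reduced AOD use (as measured by AOD testing and by self-reported frequency of AOD use"). A second primary domain follows in the same sentence, this one with four measures: "reduced sexual risk (as measured by condomless sex, self-reported number of casual partners, sex trading, and partner concurrency) in the past 30 days". That is two domains and six measures. Victimisation is then placed outside them: "An additional outcome is reduced violence and victimisation in the last 3 months".
- **Analysis, Hypothesis 1.** The primary analysis tests whether "the YWHC will reduce the primary outcome (sexual risk behaviour) as well as AOD use and victimisation relative to standard HCT". Primary is singular here and means sexual risk only.
- **Analysis, Hypothesis 2.** The programme "will improve the secondary outcome—access to HIV, STI, antenatal and reproductive health services—relative to standard HCT". Later in the same paragraph: "The primary outcome of improved access will be operationalised in two ways".

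The power section does not settle the number: "This study proposes several primary outcomes for Aim 2". It assumes a two-sided alpha of 0.05 for all its power calculations, and gives a detectable difference of 0.13 for condom use at 12 months. The Analysis section evaluates effects individually at 6 and 12 months and does not say which visit is primary.

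**The concern.** The label primary decides which result supports or refutes the efficacy claim. Here it changes between sections. Victimisation is primary in the Objectives but not in Outcome measures. AOD use is primary in both of those sections, yet falls outside the primary outcome named in Analysis. Within a domain, no single measure is singled out among two for AOD use and four for sexual risk, and no visit is named.

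Two things are at stake. First, whoever writes the final analysis must overrule at least one section of the protocol, and if that happens after results by arm are known, the choice can follow the data. Second, the detectable difference in the power section uses the full 0.05. It fits a design with one primary test, but it is too optimistic if several primary outcomes are kept and the overall error rate is held at 5%.

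**Working it through.** **1. The sections side by side**

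| Section | Sexual risk | AOD use | Victimisation | Service access |
|---|---|---|---|---|
| Objectives | primary | primary | primary | secondary |
| Outcome measures | primary (4 measures) | primary (2 measures) | additional | secondary |
| Analysis | the primary outcome | alongside | alongside | secondary and primary |

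The first three columns cannot be reconciled by interpretation. The last looks like a slip, because every other mention of access makes it secondary.

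**2. The plan's own detectable difference**

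Inputs from the power section: 225 per arm at 12 months, 24 clusters, ICC 0.01, two-sided alpha 0.05, power 0.80, proportion 0.60.

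- Mean cluster size m = 450/24 = 18.75.
- Design effect = 1 + (m − 1) × ICC = 1 + 17.75 × 0.01 = 1.1775.
- Effective n per arm = 225/1.1775 = 191.1.
- Solving the two-proportion power formula (pooled variance under the null, unpooled under the alternative) for 80% power gives 0.1346 upward from 0.60 and 0.1426 downward.

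The upward figure rounds to the stated 0.13, so the stated value is reproduced at alpha 0.05 with no division.

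**3. Number of measures**

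Outcome measures lists 2 + 4 = 6 primary measures. Counting victimisation as primary, as the Objectives do, makes 7. At two visits the upper count is 12 to 14.

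**4. Family-wise error if any one nominal p < 0.05 counted as success**

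Under no effect and independent tests, the error is 1 − 0.95^k in either direction and 1 − 0.975^k in the favourable direction only. The documents give no correlation between measures, so 0.5 between all test statistics is assumed as a second scenario.

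| Tests k | Independent, either direction | Correlation 0.5, either direction | Independent, favourable only | Correlation 0.5, favourable only |
|---|---|---|---|---|
| 6 (one visit) | 26.5% | 20.7% | 14.1% | 10.4% |
| 7 (one visit) | 30.2% | 23.0% | 16.2% | 11.5% |
| 12 (two visits) | 46.0% | 31.9% | 26.2% | 16.0% |
| 14 (two visits) | 51.2% | 34.8% | 29.8% | 17.4% |

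The favourable-only figures are about half (10.4/20.7 = 0.50) to three-fifths (29.8/51.2 = 0.58) of the two-sided ones. Their reference value is 2.5%.

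**5. Price of keeping three primary domains**

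With one measure per domain and Holm across three, the strictest step uses 0.05/3 = 0.0167. With the same effective n of 191.1:

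| From 0.60 | alpha 0.05 | alpha 0.0167 |
|---|---|---|
| Upward | 0.135 | 0.154 |
| Downward | 0.143 | 0.165 |

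The later Holm steps use 0.025 and 0.05, so this is the least favourable case.

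**The case against.** The strongest reply is that the article condenses a fuller protocol, and that a multiplicity procedure normally belongs in an analysis plan, which is not shown. That stands: the absence of a multiplicity rule is not in itself a fault here. It does not remove the point, because the conflict is between statements that are printed.

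Four stronger readings are tempting and are not supported.

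- A reader might infer that the trial can claim success on almost any chance result. The document states no success rule. Even the worst case above is 51% in either direction and 30% in favour of the intervention.
- A reader might infer that each measure will be tested at 0.05. That level appears only as an assumption of the power calculation; the Analysis section gives no level per test.
- A reader might take 14 tests as the plan. It is an upper bound. It combines the measure list of Outcome measures with the status that victimisation has only in the Objectives. The separate evaluation by visit also starts with proportions and confidence intervals, while the models handle the two visits as repeated measures.
- A reader might infer that the power statement covers only one outcome. The power section offers condom use as an example and gives a range of 0.10 to 0.13 for less common outcomes.

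It is also fair to say that choosing the primary domain is the sponsor's decision. Making sexual risk the sole primary would depart from both the Objectives and Outcome measures, which agree that AOD use is primary.

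**Conclusion.** The point holds in this form: three sections disagree on which outcomes are primary, one paragraph labels service access both ways, and no primary visit is named, while several primary outcomes are powered at an undivided 0.05. The contradiction needs no assumption. The error rates do: they apply only if any one measure at nominal 0.05 were accepted as success. On that condition the family-wise error is about 21% to 30% at one visit and up to 32% to 51% over two visits, for correlation 0.5 up to independence. The effect on the detectable difference is modest: for three primary outcomes, about 0.02 at the strictest Holm step (0.154 − 0.135 upward, 0.165 − 0.143 downward).

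**What to change.** Before any comparison by arm:

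1. Put one definition of the primary outcome or outcomes in Objectives, Outcome measures, Sample size and power, and Analysis. Name the measure for each and the primary visit. Twelve months is the visit already powered; the 6-month results can then be supportive.
2. Under Hypothesis 2, change the label on improved access from primary to secondary.
3. If one primary outcome is chosen, keep alpha at two-sided 0.05. The sponsor chooses which. If it is condomless sex, state how it relates to the proportion of condom use on which the power calculation rests, because the article does not say that they are the same variable.
4. If several domains stay primary, name one measure per domain, apply Holm across them, and restate the detectable difference (for three, about 0.154 upward or 0.165 downward from 0.60 at the strictest step).

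The cost is a change of wording while the trial is still enrolling, plus a slightly less favourable detectable difference if several primary outcomes are kept.
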